# Protocol for studying the efficiency of ChemoCalc software in helping patients to understand drug treatment costs for breast cancer: A multicenter, open-label, randomized phase 2 study

**DOI:** 10.1016/j.conctc.2021.100739

**Published:** 2021-02-11

**Keywords:** Breast cancer, Clinical trials communication, Oncology

## Abstract

Survival of patients with breast cancer can be prolonged by treatment with drugs, particularly new molecular-targeted drugs. However, these agents can be expensive and such treatments can be “an economic burden.” In this ongoing trial, we aim to assess the usefulness of ChemoCalc, a software package for calculating drug costs, to help patients understand the financial outlays. In this multicenter, randomized controlled phase 2 trial, 106 patients with advanced breast cancer will be assigned to either the “ChemoCalc” or “Usual Explanation” group. Treatment using ChemoCalc will be discussed with patients in the ChemoCalc group, whereas standard treatments, without using ChemoCalc, will be discussed with patients in the Usual Explanation group. Subsequently, the participants will decide the treatment and complete a five-grade evaluation questionnaire; those in the Usual Explanation group will receive information about ChemoCalc. Investigators will report if patients subsequently decide to change treatments. The primary endpoint will be the scores of two key questions compared between the groups: “Did you understand the cost of treatment in today's discussion?” and “Do you think the cost of treatment is important in choosing a treatment?“. The secondary endpoints will be to compare discrepancies between treatments recommended by physicians and those selected by patients, the time required for discussion, other questionnaire factors, and the relationship between Comprehensive Score for Financial Toxicity tool and treatment selection. This will be the first randomized controlled trial to assess the efficacy of software to help patients understand drug cost estimates and whether it subsequently affects treatment choice. This study will be conducted according to the CONSORT statement. All participants will sign a written consent form. The study protocol was reviewed and approved by the Clinical Research Review Board of Nagasaki University (19070801). The protocol (version 1) was designed and will be conducted in accordance with the Declaration of Helsinki (1964) and the Ethical Guidelines for Medical and Health Research Involving Human Subjects (2017). The findings will be disseminated through scientific and professional conferences, and in peer-reviewed journals.

**Trial registration:**

UMIN Clinical Trials Registry, UMIN000039904. https://upload.umin.ac.jp/cgi-open-bin/ctr/ctr_view.cgi?recptno=R000041968

## Introduction

1

More than 90,000 breast cancer cases are reported in Japan annually, with nearly 15,000 associated deaths [1]. Advanced breast cancer is treatable but not curable, and the goals of patient care are to improve symptoms, support quality of life (QOL), and prolong survival time [2]. Subtype-specific treatments, especially emerging new drugs, have gradually increased patient survival after relapse [3]. As a new targeted therapy for patients with hormone receptor-positive breast cancer, cyclin-dependent kinase (CDK) 4/6 inhibitor administered in combination with fulvestrant significantly delays deterioration in patient-reported outcomes of QOL and pain compared with fulvestrant alone [4]. However, such novel drugs can be highly expensive. “Financial toxicity” is an emerging problem, in which high out-of-pocket medical costs are associated with a decreased QOL, delayed or forgone care, or a combination of these, increasing the risk of adverse health outcomes [5,6]. Although approximately 50% of doctors and patients want to discuss out-of-pocket costs related to treatment, only 19% of the patients talk to their doctors about costs [7]. Approximately 60% of patients who have these discussions eventually decide to reduce their out-of-pocket costs. A pilot survey of oncologists reported that 42% of them assessed patient financial distress, but only 20% felt that they could intervene in financial toxicity [8].

One major barrier to patient–physician cost communication is a lack of accurate and accessible information on costs, especially out-of-pocket costs [9]. To improve price transparency, various web-based resources have been developed [10]. Eviti ADVISOR compares expected costs, outcomes, and toxicities of different treatments [11]. DrugAbacus provides current and abacus prices in an attempt to estimate the “value-based process” [12]. However, the variability in health insurance and the segmented care system make it extremely difficult to estimate out-of-pocket costs.

Japan has an excellent public health insurance system and all citizens are eligible for enrollment. The out-of-pocket costs of patients are determined based on their age (≥70 or <70 years) and income, with copayments at 10%, 20%, or 30% of the full medical costs [13]. The maximum out-of-pocket costs are 8,000–252,600 yen per month depending on the income tiers. If patient costs exceed the limit for more than 3 months in a year, the copayment is further reduced.

ChemoCalc (Nippon Chemiphar, Tokyo, Japan; https: https://www.nc-medical.com/chemocalc_web/app/) is a free downloadable software for calculating drug costs, including the costs of endocrine therapy, chemotherapy, and supportive therapies such as antiemetics. The software was created to assist doctors and pharmacists in estimating the cost of drug treatments for patients with breast cancer. We reported its usefulness in assisting patients to understand drug costs in a pilot study [14]. In this randomized controlled phase 2 trial, we aim to verify the efficiency of ChemoCalc for women with metastatic breast cancer.

## Methods and analysis

2

### Study design

2.1

In this ongoing multicenter, randomized controlled open-label phase 3 trial, we aim to evaluate the effect of ChemoCalc on the understanding of patients regarding medical costs. A study flow diagram is shown in Fig. 1. This study was approved by the Nagasaki University Hospital Clinical Research Ethical Committee (registration number 19070801), Japan. Any changes to the trial protocol will be communicated to all investigators, ethics committees, and the trial registry.

**Fig. 1 fig1:**
[figure not shown]
Study flow diagram.

### Eligibility criteria

2.2

Eligible individuals are patients aged ≥20 years and diagnosed with metastatic breast cancer, who are starting or changing a drug therapy, have two or more treatment plans presented by the attending physician, and can provide written informed consent. Both men and women can participate in this study. Patients with dementia will be excluded because they would not be able to complete a questionnaire. Patients with no out-of-pocket costs will be excluded.

### Recruitment, setting, and informed consent

2.3

Patients planning treatment for metastatic breast cancer are being recruited from Nagasaki University, National Hospital Organization Nagasaki Medical Center, National Hospital Organization Saga Hospital, and Japanese Red Cross Nagasaki Genbaku Hospital from July 31, 2019 onward. All participants are dispensed a participant information sheet and requested to provide their written consent. Participants can withdraw from the study at any time without having to provide a reason.

### Randomization

2.4

Patients will be allocated to groups using a stratified block randomization method. Each investigator will assign participants to the intervention or control group using a centralized, remote computer-generated randomizer built in Research Electronic Data Capture electronic data capture system (REDCap). The stratification factors are age (<50 years and ≥50 years) and grade of Comprehensive Score for Financial Toxicity (COST) tool (grade 0 and grade 1 or higher) [15,16]. There will be an intervention-to-control ratio of 1:1.

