### Trial endpoints

2.6

•Primary endpoint

The primary endpoint will be the comparison of scores of two key questions in the questionnaire between the two groups: “Did you understand the drug cost in today's discussion?” and “Do you think the drug cost is important when deciding on treatment?“. The questions will be rated on a five-point scale, with 1 being “not at all” and 5 being “very much."•Second'ary endpoints1.A comparison of the scores of other questions in the questionnaire (Table 1).2.A comparison of the discrepancy between physician-recommended and patient-selected treatments between the two groups (the patient-selected treatment in the Usual Explanation group is that selected before providing ChemoCalc information). Before discussion with patients, the physicians will register treatment plan ranking using REDCap. Any discrepancy will be judged based on whether the physician's first recommended treatment is selected. If there is a discrepancy, we will investigate whether the treatment choice is more expensive, equal, or less expensive than the first recommended treatment.3.A comparison of discussion time between the two groups. Discussion time is defined as the duration of one interview to discuss the treatment plans.4.The relationship between COST grade and patient-selected treatment. We will categorize the treatments chosen by patients and the first recommended treatments by the physicians into groups with and without discrepancies. In both groups, we will divide treatments selected by patients into three groups: higher, equivalent, and lower than the first recommended treatment by the physician. We will then examine whether it is related to the COST grade.5.The relationship between the upper limit of out-of-pocket costs and patient-selected treatment. We will divide the treatments chosen by patients and the first recommended treatments by the physicians into groups with and without discrepancies. In both groups, we will divide treatments selected by patients into three groups: higher, equivalent, and lower than the first recommended treatment by the physician. We will then examine whether it is related to the upper limit of out-of-pocket costs.

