### Statistical analyses

2.9

Analyses of the primary and secondary outcomes will be based on intent-to-treat and full analysis sets, which will include withdrawal from the study. Patients' clinicopathological features will be compared between the intervention and control groups. Variables will be presented as frequency (for categorical variables) and as median and interquartile range (for quantitative variables). Fisher's exact test will be used to assess associations between categorical variables, and *[Wilcoxon's rank sum test]* Mann–Whitney *U* test will be used to assess quantitative variables. All statistical analyses will be performed using SAS, EZR, and JMP software programs.

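### The primary Mann–Whitney test ignores both stratification factors and the out-of-pocket limit the trial records: still valid, but conservative if the strata are prognostic, and less precise

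*Protocol article*

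**What the plan says.** - **Randomisation (section 2.4).** Allocation is 1:1 by stratified blocks: "The stratification factors are age (<50 years and ≥50 years) and grade of Comprehensive Score for Financial Toxicity (COST) tool". COST is split at grade 0 versus grade 1 or higher, so there are four strata.
- **Primary endpoint (section 2.6).** "The primary endpoint will be the comparison of scores of two key questions in the questionnaire between the two groups". The two questions cover understanding of drug cost and the importance of drug cost, each scored 1 to 5.
- **Sample size (section 2.7).** 47 per group for a Mann–Whitney test at 0.025 per question (Bonferroni) with 90% power, raised to 53 per group for 10% withdrawal.
- **Analysis (section 2.9).** "Mann–Whitney *U* test will be used to assess quantitative variables". No stratum or covariate is named.
- **Secondary endpoint 5 (section 2.6).** "The relationship between the upper limit of out-of-pocket costs and patient-selected treatment". This needs the limit for every patient, but uses it only in relation to treatment choice.

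**The concern.** The design treats age and COST grade as important enough to balance, and the stated test then discards them. Stratified randomisation removes between-stratum variation from the difference between arms. A test that ignores the strata still counts that variation in its null variance. When the strata predict the outcome, the test therefore rejects too rarely under the null and has less power than a test that uses them.

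The out-of-pocket limit raises a related but separate question. It is not a stratification factor, so ignoring it does not make the test conservative, but it may cost precision. The Introduction says that "The out-of-pocket costs of patients are determined based on their age (≥70 or <70 years) and income" and that "The maximum out-of-pocket costs are 8,000–252,600 yen per month depending on the income tiers". It is plausible that a patient's limit bears on how important drug cost seems to them. The link with understanding of cost is less clear, and the documents give no figure for either question.

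At stake is efficiency in a trial of 106 patients, not the validity of its conclusion.

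**Working it through.** **Inputs.** From section 2.7: significance level 0.025 per question, power 90%, 47 per group, 10% withdrawal. Sidedness is not stated; two-sided is assumed, so z(0.9875) = 2.241 and z(0.90) = 1.282, sum 3.523. R² is the share of score variance explained by whatever the analysis adjusts for. It is not in the documents and is assumed to be 0.05, 0.10 or 0.20.

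**1. The plan's own figures.** 0.05/2 = 0.025, and 47/0.9 = 52.2, so 53 per group and 106 in total; both reproduce. The 47 cannot be derived uniquely, because medians and interquartile ranges do not fix a five-point distribution. Under Noether's formula, n per group = 3.523²/[6(P − 0.5)²], and n = 47 implies P = 0.5 + √(12.41/282) = 0.71. The 47 is taken as given.

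**2. Gain from adjusting for a factor not used in the randomisation.** Equivalent n = 47(1 − R²). Adjusted power at 47 = Φ(3.523/√(1 − R²) − 2.241). This is a linear-model approximation.

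| Assumed R² | 47(1 − R²) | n per group | Adjusted power |
|---|---|---|---|
| 0.05 | 44.65 | 45 | 91.5% |
| 0.10 | 42.3 | 43 | 93.0% |
| 0.20 | 37.6 | 38 | 95.5% |

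**3. Factors that are used in the randomisation.** If balance is near perfect, the plain statistic has variance of about 1 − R² instead of 1. Its actual two-sided level is 2[1 − Φ(2.241/√(1 − R²))] and its power is Φ(1.282/√(1 − R²)).

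| Assumed R² | Actual level (nominal 0.025) | Plain power | Stratified power (step 2) |
|---|---|---|---|
| 0.05 | 0.0215 | 90.6% | 91.5% |
| 0.10 | 0.018 | 91.2% | 93.0% |
| 0.20 | 0.012 | 92.4% | 95.5% |

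For the two randomisation factors the gain is therefore smaller than step 2 alone suggests: about 0.9, 1.8 and 3.1 percentage points.

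**4. Simulation.** Settings: five-point scores from a latent normal variable, 47 per arm, a three-level prognostic factor, 4,000 runs per cell. The Monte Carlo standard error is about 0.0025 for the level and 0.005 for power near 0.89. The effect is held fixed on the within-stratum scale, so here the plain test falls as R² grows, whereas in step 2 the adjusted test rises.

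| Factor in randomisation? | R² | Level, plain / van Elteren | Power, plain / van Elteren |
|---|---|---|---|
| No | 0 | 0.0235 / 0.022 | 0.89 / 0.89 |
| No | about 0.09 | 0.025 / 0.0255 | 0.87 / 0.89 |
| No | about 0.28 | 0.024 / 0.0255 | 0.77 / 0.89 |
| Yes | about 0.09 | 0.0225 / 0.030 | 0.88 / 0.90 |
| Yes | about 0.28 | 0.0085 / 0.024 | 0.81 / 0.89 |

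The 0.0085 agrees with the step 3 formula at R² = 0.277: 2.241/√0.723 = 2.636, level 0.0084. At R² of about 0.09 the loss is small, and the simulated plain level cannot be told apart from 0.025. The 0.030 for van Elteren in that row is two standard errors above nominal; in the other rows that test is at 0.022 to 0.0255.

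**The case against.** The strongest reply is that nothing here is wrong. A plain Mann–Whitney test after stratified randomisation is valid. Covariate adjustment is often left to an analysis plan, which is not shown, and R² may be close to zero. Much of this stands: the point concerns efficiency, and at modest R² the gain is small. It remains a point because the article does not leave the test open. Section 2.7 sizes the trial on the plain test and section 2.9 names it again. If the unseen documents do adjust, the article should agree with them.

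A second objection is that a proportional-odds model is a poor primary analysis here. Section 2.7 expects a ChemoCalc median of 5.0 (4.25–5.0) on both questions, so scores will pile up at the top of the scale and the lower categories will be sparse. That stands, and it is why the primary fix below is a stratified rank test.

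Three stronger readings are tempting, and the documents do not support them.

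- **That stratifying at age 50 contradicts the insurance rule at age 70.** Section 2.4 never says the age factor represents copayment. The Introduction gives the rule as background, and COST grade already brings financial burden into the randomisation.
- **That chance imbalance in payment tier would bias the result.** Random imbalance is allowed for in the test's null distribution; the simulated level with an unstratified tier was 0.024 to 0.025. With an assumed 20, 30 or 40% of patients aged 70 or over, the chance of a difference between arms of at least 10 points at 53 per arm is 18, 24 or 28% under simple randomisation. Those figures overstate it, since all such patients lie in the balanced stratum of 50 or over. They also describe age, not the out-of-pocket limit.
- **That the limit is known to predict the scores.** That is an inference. No passage quantifies it for either question.

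**Conclusion.** The point holds as one about efficiency and about matching the analysis to the design. The stated primary test ignores the two factors used to randomise and a baseline value the trial must hold. It keeps its type I error at or below 0.025, is conservative to the extent that the strata are prognostic, and gives up precision.

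The size cannot be settled from the documents. At R² of 0.05 to 0.20 the adjusted power is about 91.5% to 95.5% against a planned 90%, and part of that gain is already present in the plain test for factors balanced by the randomisation. A large loss (0.77 against 0.89 for an unstratified factor) appeared only at R² of about 0.28. These figures assume a two-sided 0.025 level, that 47 per group gives 90% power, and the linear-model or latent-normal approximations used above.

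A reader might infer that the randomisation is faulty or the trial underpowered on this account. Neither follows: the randomisation is sound, and adjustment does not raise the required sample size.

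**What to change.** Leave the randomisation and the target of 106 patients unchanged. In section 2.9, before outcome data are examined by arm:

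1. Make the primary test of each key question a van Elteren rank test stratified by age (<50, ≥50) and COST grade (0, ≥1), each at 0.025.
2. Keep the plain Mann–Whitney test as a sensitivity analysis.
3. Prespecify, as a supporting analysis, a proportional-odds model with arm, the two randomisation factors and the out-of-pocket upper limit as an ordered tier.

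If the full protocol or analysis plan already adjusts, bring sections 2.7 and 2.9 into line with it instead.

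The cost is a change of wording and slightly more analysis work, with no new data. The proportional-odds assumption touches only the supporting analysis. The primary test will capture only what the two strata explain; any gain from the out-of-pocket tier will show only in the supporting model. Timing matters: section 2.10 reports 36 patients recruited by April 2020 with recruitment ongoing, and a covariate chosen after the results are seen by arm would not be credible.

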### Assessment schedule and treatment

2.5

After consenting to participate in the study, patients will discuss treatment, determine their treatment plan, and respond to a five-point questionnaire about their decision-making process (Table 1). In the discussion phase, patients will be randomly assigned to one of the two groups, and those in the ChemoCalc group will discuss treatment with their doctors using ChemoCalc. Body surface area (BSA) will be calculated by inputting the height and weight of patients to ChemoCalc (Fig. 2a) [14]. After selecting a treatment regimen, ChemoCalc will be used to calculate the dose and cost of the drug, at 10%, 20%, and 30% (Fig. 2b) [14]. In the Usual Explanation group, doctors will discuss treatment with patients without using ChemoCalc. After the participants in the Usual Explanation group complete the five-grade evaluation questionnaire, they will receive information about ChemoCalc. Investigators will also report changes in treatment decisions made by patients after the acquisition of this information. The study period is from the time when consent is obtained until treatment drug is decided.

**Table 1 tbl1:** Questionnaire items.

1. What is your profession?
2. What is your marital status?
3. Do you have any children?
4. Do you have commercial medical insurance?
5. Did you understand drug costs in today's discussion?
6. Do you think drug cost is important when deciding on treatment?
7. Do you think you were able to independently choose your treatment during today's discussion?
8. Are you satisfied with your treatment choice based on today's discussion?
9. Did you discuss the financial burden of treatment with your doctor during today's discussion?
10. Do you think patients should talk more to health care professionals about the financial burden of treatment?
11. With whom do you want to discuss the financial burden of treatment?
12. Please tell us what concerns you currently have about your treatment.
13. (ChemoCalc group only) Was ChemoCalc easy to understand?
14. Circle the numbers that best describe the importance of choosing a treatment. The lower the score, the lower the importance.

Drug efficacy	0	1	2	3	4
Drug-related adverse effects	0	1	2	3	4
Drug cost	0	1	2	3	4
Number of visits to hospital	0	1	2	3	4
Your doctor strongly recommends treatment	0	1	2	3	4

**Fig. 2 fig2:**
[figure not shown]
Example of ChemoCalc.

### Trial endpoints

2.6

•Primary endpoint

The primary endpoint will be the comparison of scores of two key questions in the questionnaire between the two groups: “Did you understand the drug cost in today's discussion?” and “Do you think the drug cost is important when deciding on treatment?“. The questions will be rated on a five-point scale, with 1 being “not at all” and 5 being “very much."•Second'ary endpoints1.A comparison of the scores of other questions in the questionnaire (Table 1).2.A comparison of the discrepancy between physician-recommended and patient-selected treatments between the two groups (the patient-selected treatment in the Usual Explanation group is that selected before providing ChemoCalc information). Before discussion with patients, the physicians will register treatment plan ranking using REDCap. Any discrepancy will be judged based on whether the physician's first recommended treatment is selected. If there is a discrepancy, we will investigate whether the treatment choice is more expensive, equal, or less expensive than the first recommended treatment.3.A comparison of discussion time between the two groups. Discussion time is defined as the duration of one interview to discuss the treatment plans.4.The relationship between COST grade and patient-selected treatment. We will categorize the treatments chosen by patients and the first recommended treatments by the physicians into groups with and without discrepancies. In both groups, we will divide treatments selected by patients into three groups: higher, equivalent, and lower than the first recommended treatment by the physician. We will then examine whether it is related to the COST grade.5.The relationship between the upper limit of out-of-pocket costs and patient-selected treatment. We will divide the treatments chosen by patients and the first recommended treatments by the physicians into groups with and without discrepancies. In both groups, we will divide treatments selected by patients into three groups: higher, equivalent, and lower than the first recommended treatment by the physician. We will then examine whether it is related to the upper limit of out-of-pocket costs.

